## 7.7 RECRUITMENT AND RETENTION

### 7.7.1 Recruitment procedures

Eligible women who are resident in the study area will be recruited when they start attending for antenatal care in one of the ANC clinics in the participating hospitals. The study will provide dedicated study staff to deal with the additional workload. Only dedicated study staff will be involved with the recruitment and consent procedures. Where required, the trial will fund minor improvements in the infrastructure, such as the refurbishment of a dedicated study room, or pay rent to the hospital to use facilities.

### 7.7.2 Planned recruitment rate

Recruitment of 4,680 women (all gravidae) from 10 sites will require 17 months, with an additional 7 months to complete pregnancy plus infant follow-up. The recruitment rate of 280 HIV-negative women per month, or an average of 28 per site was the average recruitment in the most recent malaria in pregnancy interventions trials in Malawi and Kenya, conducted by the same teams. This corresponds to approximately 1 delivery per day per site, which is an adequate workload that helps ensure the teams are not overburdened and the data quality and completeness of follow-up is maintained to the highest standards.

### 7.7.3 Recruitment strategies for achieving target sample size

The enrolment of the target sample size is scheduled to be completed in an 18-month period, requiring an average of 260 participants per month. Each country has several proven study sites with high volume antenatal clinics that have met required sample sizes of similar magnitude before. Recruitment will be competitive between sites within a country. It is anticipated that any lag in recruitment by a site can be shifted to other sites, before being shifted to sites in the other participating countries.

## 8 METHODS: ASSIGNMENT OF INTERVENTIONS

---

### 8.1 ALLOCATION

Permuted block randomisation, stratified by site and two gravidity groups (paucigravidae [1st and 2nd pregnancies] and multigravidae) will be used to generate randomisation lists. This will be done by a statistician at LSTM who is not involved in the study. The randomisation assignments will be put in sequentially numbered, sealed, opaque envelopes, which will be opened sequentially upon enrolment of a study participant in each site. Stratification by gravidity is essential to ensure balanced distribution among study arms as this is the most important known effect modifier of susceptibility to malaria infection and the corresponding impact on pregnancy outcomes.

### 8.2 BLINDING AND UNBLINDING

#### 8.2.1 Blinding

The study will be a partially placebo-controlled involving a single placebo for AZ. To further minimise bias, we will use an objective primary outcome measure and mask all laboratory staff to the treatment assignment of individual women. The trial statistician will also be blinded regarding the treatment code when he develops the statistical analysis plan and writes the statistical programmes, which will be validated and completed using dummy randomisation codes. The actual allocation will only be provided to the study team after locking of the database and approval of the statistical

analysis plan by the independent Data Monitoring and Ethics Committee (DMEC) before they review any trial results. The study statistician conducting the interim analysis or sample size re-estimation will remain blinded throughout the analysis.

### 8.2.2 Emergency unblinding

To maintain the overall quality and legitimacy of the clinical trial, code breaks for the AZ arms will occur only in exceptional circumstances when knowledge of the actual treatment is absolutely essential for further management of the participant. Site investigators will be encouraged to discuss with the principal and chief investigators if he/she believes that unblinding is necessary. If unblinding is deemed to be necessary, the investigator will follow a standard operating procedures that will be developed specific for this trial describing the system for emergency unblinding. The unblinding shall be performed by the sponsor for that specific patient by the sponsor before notification of the SUSAR to the ethics committee and regulatory authority of all participating countries. As far as possible, the blinding shall be maintained for the trial staff, investigators and the biostatistician responsible for data analysis and interpretation. Consequently, the SUSAR and required unblinding should therefore be processed by a person assigned by the sponsor who is not involved in the conduct of the trial. The Data Monitoring and Ethics Committee (DMEC) may perform the duties required in case of unblinding to ensure that the sponsor and the trial team remain blinded.

Because the unblinding will be on an individual basis, the blinding of other participants is not affected. All Investigators are encouraged to maintain the blind as far as possible following the subsequent follow-up of the participant. The actual allocation will NOT be disclosed to the participant and/or other study personnel including other site personnel, monitors, corporate sponsors or project office staff; nor will there be any written or verbal disclosure of the code in any of the corresponding participant documents, with the exception of correspondence between the principal or chief investigator and the safety monitor or the DMEC chair. All code breaks (with reason) will be reported as they occur on a dedicated case report form. Unblinding will not necessarily be a reason for study drug discontinuation unless it is absolutely essential for the management of the participant.

## 9 METHODS DATA COLLECTION, MANAGEMENT AND ANALYSIS

---

### 9.1 PROCEDURES FOR ASSESSING EFFICACY AND SAFETY PARAMETERS

#### 9.1.1 Efficacy

##### 9.1.1.1 SGA-LBW-PT

New-borns will be weighed within 24 hours of delivery using digital scales ( $\pm 10$  gr) and LBW defined as  $< 2,500$ g. Gestational age will be assessed using ultrasound dating at enrolment and preterm (PT) defined as  $< 37$  weeks' gestation. Small for gestational age (SGA) will be defined as birthweight below the tenth percentile for a given gestational age and sex, using the new INTERGROWTH reference population. This will also allow the calculation of Z-scores.

##### 9.1.1.2 Pregnancy outcome and neonatal death

Foetal loss will be assessed monthly at scheduled ANC visits. If women do not return they will be contacted by mobile phone and/or visited at home to document this. Neonatal death will be assessed at the 6-week follow-up visit.

### 9.1.1.3 Malaria infection

Malaria infection will be assessed at the scheduled monthly ANC visits and at delivery by taking dried blood spots for malaria diagnosis by molecular detection methods such as PCR or LAMP or Illumina®-based sequencing. Standard light microscopy will be used to evaluate malaria smears and RDTs will be used for point-of-care diagnosis in febrile women or women with a history of fever in the last 48 hours to measure the incidence of clinical malaria, with RDT-positivity defined as either pLDH or HRP2 antigen positivity. At delivery, samples will be taken for molecular diagnostics (henceforth referred to as PCR), microscopy, and placental histology.

### 9.1.2 Safety

The presence of congenital abnormalities and jaundice will be assessed at delivery, day 7, and at 6 to 8 weeks. The vital status of participants will be recorded at each scheduled and unscheduled visit, and through follow-up phone calls and home visits if women do not attend the scheduled visit. Maternal mortality will be defined as the death of a woman while pregnant or within 42 days of termination of pregnancy, irrespective of the duration and site of the pregnancy, from any cause related to or aggravated by the pregnancy or its management but not from accidental or incidental causes. A verbal autopsy questionnaire will attempt to determine the cause of death.

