##### 4.1.1.2 Safety

Treatment with DP has been shown to be safe in the 2nd and 3rd trimester of pregnancy. A single course of DP is safe for use in the 2nd and 3rd trimesters, and is recommended by WHO for treatment of malaria in the 2nd and 3rd trimester and has been the first-line treatment for this indication in Papua, Indonesia, for over 10 years. The main safety concern is a dose-dependent QTc prolongation associated with piperaquine, similar to that observed with other antimalarials like chloroquine, but less severe than with halofantrine and quinine. Clinical data do not suggest any association with arrhythmias when used as a single three-day course for treatment. The experience, however, with monthly dosing is more limited; approximately 1,000 women have received either 3-course or monthly IPTp-DP in Kenya, Uganda, and an ongoing IPTp-DP trial in Indonesia (STOPMIP-Indonesia).

There has been no indication that IPTp-DP is associated with an increased risk of congenital malformation or pregnancy loss (the existing evidence in Africa suggest a 61% [95% CI 12-83] reduction in the risk of foetal loss compared to SP [fixed effect meta-analysis conducted for this application]). Because of its slow elimination, monthly doses of DP could result in dose accumulation of piperaquine. Nevertheless, there is no evidence to date that the risk of QTc

prolongation increases with each subsequent monthly course, likely because piperazine-associated QTc prolongation is transient and lasts for a few days only. The magnitude of transient QTc prolongation remained constant and was similar after  $\geq 12$  monthly courses compared to a single course in a study of Ugandan children provided with 18 monthly courses of DP from 6 to 24 months of age.

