#### 9.1.2.1 Procedures for cardiac monitoring

Cardiac monitoring will be conducted in 160 women; 80 per DP arm.

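### The only named outcome for death of the woman is filtered by cause, with SP versus DP open and no masking of the cause judgement stated; add all-cause death by arm

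*Protocol*

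**What the plan says.** Section 7.4.2.2 lists four safety outcomes: QTc prolongation, congenital malformations, maternal mortality, and other SAEs and AEs. The summary table in 2.3.1 has the same list. Neither names death of the woman from any cause.

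Section 9.1.2 defines maternal mortality as "the death of a woman while pregnant or within 42 days of termination of pregnancy", and adds the restriction "from any cause related to or aggravated by the pregnancy or its management but not from accidental or incidental causes". On how cause is found, it says: "A verbal autopsy questionnaire will attempt to determine the cause of death". It does not say who then decides whether a death meets the restriction.

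On masking, 8.2.1 says "The study will be a partially placebo-controlled involving a single placebo for AZ" and that the trial will "mask all laboratory staff to the treatment assignment of individual women". The trial statistician is blinded while preparing the analysis plan and programmes, and 9.1.2.1.1 has ECGs read off-site by blinded clinicians. Assessors of cause of death are not mentioned.

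Section 4.1.1.2 says: "The main safety concern is a dose-dependent QTc prolongation associated with piperaquine".

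**The concern.** When a comparison of deaths is filtered by cause, its result depends on the judgement that does the filtering. If the person judging can know the arm, the filter can remove deaths from one arm more readily than from another. The bias could run either way: it could hide a difference or create one.

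This matters here because the named concern with DP is cardiac. A sudden death in the community may leave little evidence beyond a verbal autopsy, so its classification could be uncertain. A count of all deaths needs no such judgement, and the trial already collects what is needed to make one.

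**Working it through.** The plan states no figure on this point, so none can be reproduced. The check sets the sections side by side; the arithmetic at the end is for scale only.

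1. **What decides whether a death counts.** Under 9.1.2 the timing is objective (pregnancy plus 42 days) but the cause restriction is a judgement. Verbal autopsy is the only source of cause named there.

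2. **Who can know the arm.** The only placebo described in 8.2.1 is for AZ. Table 2 gives SP on one day and DP on three days, with no DP or SP placebo, and 8.2.2 describes code breaks for the AZ arms only. Section 7.3.1.4.1 speaks of identical, blinded packaging, and 14.2 mentions a DP placebo, but the regimens in Table 2 still reveal SP versus DP. DP versus DP+AZ is masked, so the concern is confined to SP against the DP arms.

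3. **Where a death judged incidental goes.** Under 10.2.1.3 any event resulting in death is an SAE. Other SAEs and AEs are a listed outcome (7.4.2.2), and safety data go to the DMEC and sponsor (10.2.4.3). The analysis named for SAEs in 9.3.2.2 is a Poisson comparison of their number, in which a death weighs the same as any hospital admission. Expedited reporting (10.2.4.1) applies to events that are unexpected and at least possibly related; the responsible study clinician assigns causality (10.2.4), with no masking stated. Other SAEs go into an aggregated report, annual unless more is required (10.2.4.2).

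4. **Whether all-cause death can be derived.** Section 9.1.2 has vital status recorded at every visit and by phone or home visit for women who miss one. The last visit is at six to eight weeks after birth (7.5.5.2), that is 6 × 7 = 42 to 8 × 7 = 56 days, which reaches the end of the 42-day window.

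5. **In whom it would be counted.** Section 9.3.1.1 makes the safety population a subset of the ITT population, and the ITT population requires a valid outcome. Read literally, a dosed woman who dies without a valid outcome is outside the safety analysis, so an all-cause outcome needs its own denominator.

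6. **Scale.** Inputs: 4,680 women, 1,560 per arm (7.6.1.2); 160 women with ECGs ("Cardiac monitoring will be conducted in 160 women; 80 per DP arm"); an assumed death risk of 0.1% to 0.4%.
   - Expected deaths: 4,680 × 0.001 = 4.7; 4,680 × 0.004 = 18.7. So about 5 to 19 over three arms.
   - Weight of one death: 1/19 = 5%; 1/5 = 20%.
   - ECG coverage of the DP arms: 2 × 1,560 = 3,120; 160/3,120 = 5.1%, leaving 3,120 − 160 = 2,960 women without study ECGs.
   - If no deaths are counted, the exact one-sided 95% upper limit on risk is 1 − 0.05^(1/n): 0.19% for n = 1,560 and 0.096% for n = 3,120.
   - Illustration only: with 9 deaths among 3,120 women on DP and none among 1,560 on SP, Fisher's exact test gives p = 0.034. If two of the nine are judged incidental, 7 against 0 gives p = 0.104.

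**The case against.** The strongest reply is that no death disappears. It is an SAE whatever its cause, SAEs are compared by arm, and the DMEC receives the safety data and can see it unblinded. This stands. A reader might infer that a sudden cardiac death on DP could drop out of the safety data; the protocol does not support that. Such a death could lose its place in the mortality comparison only.

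Nor does the definition clearly exclude such a death. It covers deaths related to the management of the pregnancy, which can be read to include one attributed to IPTp. This also stands, but the death then counts only if someone already attributes it to the drug, which is a weak basis for detecting an unrecognised harm.

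A reader might also infer that only laboratory staff are masked, or that classification rests on verbal autopsy alone. Neither is supported. The statistician and the off-site ECG readers are blinded too. Records of all SAEs are reviewed (10.2.2), causality assessment weighs alternative causes and may involve the DMEC (10.2.3), and each country has a safety monitor (10.4.1). None of these sections, however, states masking of the cause judgement.

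QTc prolongation has its own outcome and blinded ECG reading, so mortality is not the trial's main instrument for cardiac toxicity. That is fair, but the ECG study covers 5.1% of women in the DP arms.

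Finally, a cause-restricted maternal death definition is a conventional choice, and an analysis plan could tabulate all deaths. Using the definition is not an error. But the protocol itself fixes the named outcomes, and all-cause death is not among them.

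**Conclusion.** The point holds as a cheap improvement of minor to moderate importance. The only named mortality outcome for the woman depends on a cause judgement for which no masking is stated, in a trial open for SP versus DP. A death judged incidental remains an SAE, but no named comparison separates deaths from other SAEs.

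The size rests on an assumed death risk, since the protocol gives none: about 5 to 19 deaths, each 5% to 20% of the total. Nothing in the protocol shows how many deaths would be judged incidental, or that the judgement would differ by arm. The case rests on the opportunity for bias and the ease of avoiding it.

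**What to change.** In 7.4.2.2 and 9.1.2, add as a safety outcome death of the woman from any cause, from first study dose to 42 days after the end of pregnancy, compared by arm. Count it in all women who received at least one dose, whether or not they have a valid primary outcome, and say so explicitly because of the wording of 9.3.1.1. Keep the present maternal mortality definition as a reported sub-classification of these deaths.

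The cost is one definition and one extra outcome row; vital status is already collected. The downside is that the all-cause figure will include some deaths unrelated to treatment, which the sub-classification will show. Masked review of cause would strengthen the sub-classification but needs extra staff; the all-cause comparison does not depend on it.

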#### 9.1.2.1 Procedures for cardiac monitoring

Cardiac monitoring will be conducted in 160 women; 80 per DP arm.

##### 9.1.2.1.1 Electrocardiogram (ECG)y

ECGs will be conducted prior to the first dose and then again 4-6 hours after the 3rd dose of each course of IPTp containing DP by dedicated staff at the clinic and results read by local clinicians; All ECGs will also be read off-site by blinded clinicians and discrepancies resolved by an experienced cardiologist, such as those from Cardibase, Banook Group, Nancy, France. Confirmed QTc values >480ms will be considered as contradiction for subsequent IPTp courses with DP. In such events, women will continue in the study but will receive IPTp with SP instead of DP. The results of the external expert reading of ECGs will be available to the site PI or assigned clinical staff within hours of reading. ECGs and results will be available on a secure server (provided by the study or by the external experts, e.g. by Cardibase). The external experts and the site PI will be alerted by e-mail as soon as the ECGs and results respectively have been uploaded onto the server. Feedback to participants will be provided on site. This will be within minutes after the ECG has been taken if the automated output from the ECG machine suggests the ECG is normal. If the output suggests any other variation, results will be provided within 1 to 2 hours following confirmatory reading by the study clinician. If the subsequent results of the expert reading disagree with the initial reading on site, and if these are of clinical relevance to the patient, results will be shared with the participant when she returns for her follow-up ECG 2 days later if it pertains to the baseline ECG prior to each course. If the expert results relate to ECGs taken after the 3rd dose of each course (Tmax), the results shall be provided to the participant at the next scheduled antenatal visit prior to the first dose for that visit. In the event of any findings with clinical significance, participants shall be traced and requested to report to the study clinic as soon as possible for communication of the findings and appropriate clinical management.

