| 
Visit 1: Pre-screening interview, Screening, Consent, Enrolment, Randomisation, and Allocation. First IPTp treatment dose given under direct observation.
 
Visits 2 to 4: Monthly IPTp treatment and ANC follow-up visits.
 
Visit 5: Delivery visit. To be conducted as soon as possible after birth without interrupting the initiation of breastfeeding or any necessary care required to the mother or newborn. A surface examination shall be conducted to assess for external congenital abnormalities.
 
Visits 6 and 7: Routine postnatal care, physical examination and follow-up of the mother-newborn pair.
 
a. Visits spaced approximately one month apart. The max. number of scheduled visits depends on the gestational age at enrolment (estimated median of 3 to 5).
 
b. Pre-study screening can take place any time women start visiting the ANC; i.e. even prior to 16 weeks gestation, but the intervention can only start at 16 weeks.
 
c. Cardiac safety monitoring; One ECG prior to 1st dose of each course and one 4-6 hours after the 3rd dose of each course (subgroup 160 women, 80 in each DP arm).
 
d. The first dose (day-0) always given under direct observation and subsequent 2 doses are to be taken at home (day-1 and day-2).
 
e. Baseline ultra sound scans in all women to assess the gestational age. Additional ultrasound scans to determine foetal growth at scheduled visits occurring at the approximate gestational ages of 25-28 weeks and 32-35 weeks (subgroup only), or otherwise at the nearest scheduled monthly visit.
 
f. Vomiting and other adverse events (AEs) occurring within 30 minutes of the first dose will be assessed. Subsequent AEs will be captured though passive surveillance. Participants will be encouraged to report to the study clinic for any subsequent AEs that may arise after each study visit at any time before the next study visit.
 
g. Enrolment & delivery blood sample by venepuncture (VP) (up to 10 mL) or finger prick (~250µL): All women all sites: haemoglobin level, HIV test (unless known to be HIV+), syphilis, malaria smear, dried blood spots (DBS) for molecular malaria diagnostics (not for point of care, DBS for multi-pathogen antibody assays and drug resistance. Sub-group (venepuncture): Nutritional biomarker including leptin, adiponectin, aflatoxin-albumin adduct (AF-alb) levels; antibody and cell mediated immune responses to malaria and other pathogens; biomarkers of placental function, inflammation and gestational age; malaria diagnostics, and drug levels. Remaining red cell pellets will be stored.
 
h. Interim study visits blood sample by venepuncture (up to 10 mL) or finger prick (~250µL): Same assays as for baseline, with the exception of syphilis. HIV testing and nutritional biomarkers will be done once in third trimester only during one of the last scheduled visits prior to delivery.
 
i. Umbilical cord blood (CB) sample (7 mL in subgroup and 5 mL in all others): Haemoglobin level, malaria molecular diagnostics, antibody and cell mediated immune responses to malaria and other pathogens, and nutritional biomarkers including leptin, adiponectin and drug levels. Heel prick (HP) sample (~ 500 microl) in all babies with fever or other symptoms for malaria RDT, microscopy and dried blood spot, and in subgroup of asymptomatic infants for immunological assays.
 
j. Venepuncture 2 ml blood sample taken 4-6 hours after last dose of each course (cMax) for biochemistry and drug levels (subgroup of 160 women in ECG component)
 
k. Stool sample at enrolment and last scheduled antenatal ANC visit prior to delivery in subgroup (n~1,464). Postnatally, only new-born stool sample shall be collected.
 
l. Placental samples at delivery/termination of pregnancy: placental section for histopathology, amnion roll, placental impression smear, maternal placental blood for malaria diagnostics (not for point of care), drug levels, and cord blood (i.e. newborn's side) (see cord blood sample).
 
m. Maternal anthropometric measurements: Enrolment: height; All visits: Weight, and MUAC. Sub-group only: delivery, 1 and 6-8 postpartum: skinfold thicknesses (SFTs), hip and waist circumference, bioelectrical impedance analysis and deuterium analysis (FTIR).
 |   |   |                |

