### **7.3.1.2 Administration of the study drugs**

#### **7.3.1.2.1 Day-0**

All doses on day-0 will be provided as directly observed therapy. Participants will be given some clean water for swallowing the tablets. Women will then be observed for thirty minutes. If vomiting occurs during this time the full dose will be repeated. If the participant vomits again after the repeat dose she will be provided with unblinded standard IPTp-SP and not be issued the subsequent doses for that course (if any).

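### Cardiac sub-study: the >480 ms QTc rule is scoped to later DP courses only, so it does not cover home doses 2 and 3 after an abnormal pre-dose ECG

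*Protocol*

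**What the plan says.** Table 1, footnote c, sets the ECG times: "One ECG prior to 1st dose of each course and one 4-6 hours after the" third dose of each course, in 80 women per DP arm. Footnote d sets where the doses are taken: "The first dose (day-0) always given under direct observation and subsequent 2 doses are to be taken at home (day-1 and day-2").

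Section 9.1.2.1.1 has each ECG read locally and off-site by experts. It gives one numerical limit: "Confirmed QTc values >480ms will be considered as contradiction for subsequent IPTp courses with DP". Women above it stay in the study and are given SP in place of DP.

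If the expert reading disagrees with the site reading and matters to the patient, the section sets routine feedback times. For the pre-dose ECG, "results will be shared with the participant when she returns for her follow-up ECG 2 days later if it pertains to the baseline ECG"; for the post-dose ECG, feedback waits for the next antenatal visit. The section then closes with a general provision: "In the event of any findings with clinical significance, participants shall be traced and requested to report to the study clinic as soon as possible", so that the finding can be communicated and managed.

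Sections 7.3.2.2 and 7.3.5.1 allow withdrawal from study drug on safety grounds, at the judgement of the investigator, the safety monitor or the DMEC. Neither names a QTc value.

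**The concern.** A threshold that bars only later courses is complete for an ECG taken after dose 3, because no dose of that course remains. It is incomplete for an ECG taken before dose 1. If the expert reading confirms a value above 480 ms once the woman has gone home with her tablets, the rule removes DP from next month's course and is silent on tomorrow's dose.

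The protocol's own account of the drug makes the current course relevant. Section 4.1.1.2 states: "The main safety concern is a dose-dependent QTc prolongation associated with piperaquine". It adds that the "QTc prolongation is transient and lasts for a few days only". For a woman who starts above the limit, each dose still to be taken in the running course adds exposure within that window. At stake is the safety of individual women in the sub-study and the consistency with which sites act. The efficacy comparison is not involved.

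**Working it through.** No arithmetic decides this point. The check is to line up the ECGs, the doses and the rules.

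**Timeline of one DP course (Table 1 footnotes c and d; sections 7.3.1.2.2 and 9.1.2.1.1)**

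| Time | Event | Doses of this course still to come | Covered by the >480 ms rule as worded? |
|---|---|---|---|
| Day 0, before dose 1 | Pre-dose ECG | 3 | Not on the literal wording |
| Day 0 | Dose 1, observed in clinic | 2 | No |
| Day 1 | Dose 2, at home | 1 | No |
| Day 2 | Dose 3, at home | 0 | Not applicable |
| Day 2, 4-6 h after dose 3 | Follow-up ECG; routine feedback on the pre-dose over-read | 0 | Yes, for later courses |

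**What this shows**

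1. The number of doses that could still be withheld depends on when the confirmed result reaches the site: 2 if before dose 2, 1 if between doses 2 and 3, and 0 after dose 3. Section 9.1.2.1.1 says the expert result reaches the site within hours of being read. It ties neither the reading nor the result to a dose, and it does not hold dose 1 for the expert result.
2. Under the routine feedback sentence taken alone, the woman learns of a discordant pre-dose reading when 0 doses remain.
3. Under the tracing sentence she is recalled at once. Section 9.1.2.1.1 does not say that a confirmed value above 480 ms always falls under that sentence. Sites must infer it.
4. The protocol does write an explicit rule for the rest of a course in another situation. Under section 7.3.1.2.1, a woman who vomits a repeat dose is handled as follows: "she will be provided with unblinded standard IPTp-SP and not be issued the subsequent doses for that course (if any"). The QTc rule has no counterpart.

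**Sub-study size, needed for the cost of the fix (section 7.6.3)**

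- Inputs: difference 10 ms, SD 25 ms, 90% power, two-sided alpha 0.05, paired test.
- Normal approximation: n = ((1.960 + 1.282) × 25 / 10)² = 65.7, so 66. The paired t-test gives 68 (power 0.902), which matches the protocol.
- Loss allowance: 68 / (1 − 0.15) = 80 per arm, also as stated. The margin is 80 − 68 = 12 women per arm.

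**The case against.** The strongest case against has four parts.

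*The section already distinguishes two levels.* A reader might infer that the routine feedback sentence and the tracing sentence contradict each other. The text does not support that. The tracing sentence comes last, applies to any ECG finding, and is aimed at clinical management as well as communication. It reads naturally as an override of the routine timings. This part of the objection stands. What remains is that the protocol never says which side of the line a confirmed value above 480 ms falls on.

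*Nothing prevents stopping the drug.* A reader might infer that a woman above the limit must finish her course. That is also unsupported: sections 7.3.2.2 and 7.3.5.1 and the management clause in 9.1.2.1.1 all permit withdrawal. This stands too, but the protocol chose to fix a number for later courses, and leaving the running course to judgement gives the more immediate decision the looser rule. One could also read the word subsequent relative to the ECG, so that the course about to start is covered. Even then, nothing states what happens to doses 2 and 3 if confirmation arrives after dose 1.

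*The gap is narrow.* Automated output is available within minutes, a suspicious trace is read by the study clinician within 1 to 2 hours, known heart ailment is an exclusion, and section 7.3.4.3 already plans phone reminders for doses 2 and 3. For an over-read to matter, the site must have missed a value that the expert places above 480 ms. This keeps the point minor.

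*Later courses matter as well.* Each further monthly course would bring its own transient prolongation, and the existing rule prevents all of those. That is correct. The rule is useful where it applies; the point is only that it stops short of the course in progress. The vomiting rule is also an imperfect parallel, since vomiting is seen in clinic before the home doses are issued.

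**Conclusion.** The point holds as a scoping fault in one safety rule: the sole QTc threshold is written for later courses, although one of the two ECGs it must serve is taken before a course whose last two doses are swallowed at home. It is minor. It concerns 160 women, several safeguards already operate, and it has no bearing on the primary endpoint, the trial's sample size or the type I error rate.

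A reader might take the two doses out of three left uncovered as a measure of harm. It is not; it only restates the dosing schedule. The protocol gives no frequency for pre-dose values above 480 ms or for disagreement between site and expert, so no number of affected women can be claimed. The conclusion rests on the literal wording of section 9.1.2.1.1 and on the protocol's own description of the QTc effect as dose-dependent and short-lived.

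**What to change.** Amend section 9.1.2.1.1 in a few sentences:

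- A confirmed pre-dose QTc above 480 ms also contraindicates the current DP course: do not start it, or withhold its remaining doses if it has begun.
- Such a value always counts as a clinically significant finding and triggers immediate phone contact and tracing once the site has the result.
- State whether SP is given in place of the interrupted course.
- Keep the 2-day and next-visit feedback for over-reads that need no action.

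The contact details (section 7.3.4.2), dose-day phone reminders (section 7.3.4.3) and tracing are already planned, so little new machinery is needed. The cost is a few incomplete DP courses and some post-dose ECGs that are missing or not comparable. Women with a confirmed value above 480 ms already leave DP for later courses, so the added loss is that one course's post-dose ECG. The margin of 12 women per arm was set aside for loss to follow-up and should not be treated as spare capacity for this, but the number of such cases should be small.
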